#### Cost-effectiveness

Finally, the ICER will be calculated by dividing incremental costs by incremental health gains and is by consequence expressed as €/QALY gained. This outcome can thus be interpreted as the additional amount of costs needed for the blended physiotherapy program to gain one additional QALY compared to the usual care program. The robustness of the results will be assessed by bootstrapping (> 1000 samples) and be presented on a cost-effectiveness plane. The results will consist of a base case analysis taking into account only the direct medical costs and an extended analysis taking into account both direct and indirect costs.

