One way to provide these extra elements is through a smartphone application. In the last decade, computer and smartphone applications increasingly found their way into medicine and physiotherapy treatment. Recently, the COVID-19 pandemic has shown that low-contact treatment provided from a distance through applications and videoconferencing can be used as a substitution of or addition to face-to-face clinical care for several conditions [24–26]. Telerehabilitation and internet-based psychological counselling have already proven to be as effective as standard practice in relieving pain and disability in a variety of musculoskeletal conditions [27, 28] and in reducing distress in case of tinnitus [29]. The use of a smartphone application might provide additional support to motivate the patient to perform daily exercises in order to increase exercise compliance. Furthermore, it can be used to provide psychological tinnitus counselling.

Therefore, the aim of this single-blind non-inferiority two-arm parallel group 1:1 randomised controlled trial is to investigate the effectiveness and cost-effectiveness of a blended physiotherapy program for ST, including a smartphone application designed to increase therapy compliance and provide tinnitus counselling. It is hypothesised that the blended physiotherapy program will at least be as effective as the standard physiotherapy care and that this new intervention will reduce both direct and indirect costs related to ST.

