### Sample size and power

The study is designed as a non-inferiority trial of a continuous response variable comparing independent control and experimental subjects. The primary outcome is the change in TFI from baseline to 1-month follow-up. We hypothesise that there is no significant difference between the control and experimental group for this outcome. A non-inferiority margin is chosen at 6.5 points, being half of the minimally clinically important difference [66]. Assuming a standard deviation of 20 points (SD found in international literature [67] as well as in previous performed own studies [14, 18]) and a significance level (*α*) of 0.025, an achieved sample size of 150 patients per group is required to have 80% power to show non-inferiority using a one-sided, independent samples *t*-test. Considering a possible 10% drop-out, based on previous studies in ST [14, 37], 167 patients will be recruited into each group. Hence, a total of 334 patients will be recruited for the study.

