#### Cost -effectiveness analysis (CEA)

The outcome of the CEA is the incremental cost-effectiveness ratio (ICER) of the blended physiotherapy program compared to the usual care program. The ICER is calculated as incremental costs divided by incremental effects. The analysis thus consists of two components: (1) incremental costs and (2) the incremental health outcomes (effects).

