The current standard physiotherapy treatment is, although effective, costly and time consuming, especially in case of recurrent complaints where patients often need several follow-up consultations and additional treatment. The longevity of the need of treatment due to recurrent complaints leads to high direct health care costs [8, 9]. Furthermore, also indirect costs, such as work absenteeism and productivity losses are high in these patients [8, 9]. Our investigated blended physiotherapy program aims to decrease the patient’s need for in-clinic treatment, without reducing the effectiveness of the treatment. The alleviation of tinnitus improves the quality of life and, as a consequence, is expected to increase productivity and reduce absenteeism. In addition, the blended physiotherapy program will reduce the need for face-to face clinical care and is expected to improve the patient's self-management skills, rather than depending on the therapist’s care in case of recurrent symptoms. All these factors are expected to contribute to a significant decrease in both direct and indirect costs due to somatic tinnitus. The proposed blended physiotherapy program has the potential to be a valuable alternative for the current standard care, with a better cost-effectiveness without decreasing the effectiveness of the treatment.

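### The ICER is the named cost-effectiveness outcome, but its stated reading as a price per QALY gained does not fit the cost saving that the trial expects

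*Protocol article*

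**What the plan says.** All references are to the Protocol article. The section on the cost-effectiveness analysis opens: "The outcome of the CEA is the incremental cost-effectiveness ratio (ICER"). Under Cost-effectiveness, "the ICER will be calculated by dividing incremental costs by incremental health gains", in euro per QALY gained, and the result is to be read as "the additional amount of costs needed for the blended physiotherapy program to gain one additional QALY compared to the usual care program". Robustness is to be assessed with more than 1000 bootstrap samples shown on a cost-effectiveness plane. There is a base case with direct medical costs only and an extended analysis that adds indirect costs.

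The expected result is described elsewhere:

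- **Cost.** The Background hypothesises that "this new intervention will reduce both direct and indirect costs related to ST".
- **Effect.** The Background hypothesises that "the blended physiotherapy program will at least be as effective as the standard physiotherapy care". Sample size and power says of the change in TFI: "We hypothesise that there is no significant difference between the control and experimental group for this outcome".
- **Both together.** The Discussion sees the blended program as an alternative "with a better cost-effectiveness without decreasing the effectiveness of the treatment".

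**The concern.** A ratio of cost difference to QALY difference can be read as a price only when the new program costs more and gains QALYs. The protocol expects the new program to cost less. The one reading it gives for its named outcome therefore applies to a result that it does not expect.

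Two separate things are at stake.

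- **Meaning.** A less costly, less effective result gives a positive ratio. The protocol's sentence would present that ratio as the price of a QALY gained, when it is the saving per QALY given up.
- **Stability.** If the QALY difference lies close to zero, a small change in the denominator can flip the sign of the ratio and change its size many times over.

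Cost-effectiveness is one half of the trial's stated twofold aim, so the quantity that answers it should stay readable if the hypotheses turn out to be true.

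**Working it through.** **1. What the design assumes about effect.** Inputs from Sample size and power: margin 6.5, SD 20, one-sided alpha 0.025, power 80%. With a true difference of zero, n per group = 2 × (1.960 + 0.842)² × 20² / 6.5² = 148.6, so 149 by the normal approximation. The t-test at 150 per group has 80.1% power. Then 150 / 0.90 = 166.7, so 167 per group and 334 in total. The stated figures reproduce with a true TFI difference of zero.

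**2. The four quadrants.** This step tests the reading and does not depend on variances. For illustration, take a cost difference of 200 euro and a mean utility difference of 0.01 (both assumed). The utility difference is held over 25 weeks: 12 weeks of treatment plus up to 13 weeks to the second follow-up visit. The QALY difference is 0.01 × 25/52 = 0.0048, and 200 / 0.0048 (unrounded) = 41,600. Net monetary benefit (NMB) is threshold × QALY difference − cost difference, here at an assumed 20,000 euro/QALY, so 20,000 × 0.0048 = 96 (unrounded).

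| Cost | QALYs | ICER | Meaning | Does the protocol's reading hold? | NMB |
|---|---|---|---|---|---|
| higher | more | +41,600 | price per QALY gained | yes | 96 − 200 = −104 |
| lower | more | −41,600 | dominance | no, no extra cost is needed | 96 + 200 = +296 |
| lower | fewer | +41,600 | saving per QALY lost | no, the meaning is reversed | −96 + 200 = +104 |
| higher | fewer | −41,600 | dominated | no | −96 − 200 = −296 |

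Each ICER value appears twice with opposite meanings, while NMB separates all four cases. A negative ICER also cannot be ranked by size. With the same saving and a larger utility gain of 0.05, the QALY gain is 0.05 × 25/52 = 0.0240 and the ICER is −200 / 0.0240 = −8,320 (unrounded denominator). The better result has the number nearer zero.

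Under the cost hypothesis the result lies in one of the two lower-cost rows. The stated reading fails in both.

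**3. Stability if the true QALY difference is zero.** Assumptions that are not in the documents: SD of mean utility 0.10 to 0.25, saving 200 euro, cost SD 500 or 1500 euro, costs and QALYs independent. There are 150 patients per group.

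- SE of the QALY difference = SD × (25/52) × √(2/150). This is 0.006 at SD 0.10 and 0.014 at SD 0.25.
- The probability that the QALY difference is negative is 50%. At cost SD 500, almost all 200,000 simulated results are cost-saving, split about evenly between dominance (negative ICER) and savings with QALYs lost (positive ICER).
- The central 95% range of the ICER runs from about −230,000 to +225,000 at its narrowest up to about −619,000 to +642,000 euro/QALY.
- A simpler check with other assumed values (SD 0.15, horizon 0.45 year, fixed saving of 300 euro) gives SE = 0.15 × 0.45 × √(2/150) = 0.0078 and a range of about −614,000 to +604,000.

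**4. Stability if the blended program gains QALYs.** With a constant utility gain the horizon cancels, so P(QALY difference < 0) = Φ(−gain / (SD × √(2/150))).

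| True utility gain | P(QALY difference < 0), SD 0.10 to 0.25 |
|---|---|
| 0.01 | 19% to 36% |
| 0.02 | 4% to 24% |
| 0.03 | 0.5% to 15% |
| 0.05 | 0% to 4% |

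The instability fades as the gain grows. The misreading does not, because a saving with a clear QALY gain still gives a negative ratio.

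**5. NMB under the assumptions of step 3.** SE(NMB) = √[(threshold × SE of QALY difference)² + (SE of cost difference)²]. It is about 125 to 327 euro at an assumed 20,000 euro/QALY and 229 to 582 euro at 40,000. It is finite and reads in one direction.

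**The case against.** The strongest reply is that the plan already contains the remedy for an ambiguous sign. The bootstrap results go on a cost-effectiveness plane, which stays well defined when the QALY difference crosses zero and which separates dominance from savings with QALYs lost. The cost and QALY differences are also calculated on the way to the ratio, and the disputed sentence is the usual textbook gloss on the unit. This stands in part. The plane limits the ambiguity for a careful reader. It does not change which quantity is named as the outcome, steady that quantity, or correct the sentence attached to it.

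Three stronger readings are tempting, and the documents do not support them.

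- **That the protocol plans an unusable bootstrap interval for the ICER.** It promises bootstrapping and a plane, and no interval for the ratio.
- **That it expects a QALY difference of zero.** The no-difference hypothesis concerns TFI at 1 month, and the Background says at least as effective. The blended arm also receives app-based tinnitus counselling that controls do not, so a QALY gain is compatible with the text. A near-zero difference is an inference from the TFI hypothesis and the roughly half-year horizon.
- **That it lacks a threshold or acceptability curve.** These may sit in a health-economic plan that is not shown. Their absence is not the point; the point is the outcome and reading that this document does state.

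It is also fair to say that the ICER ranges above are not a measure of imprecision. With a zero true difference they narrow as the utility SD grows. They show only that the ratio behaves badly.

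**Conclusion.** The concern holds in two parts of unequal strength.

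The first is firm and needs no outside figure. If costs fall as hypothesised, the stated reading of the named outcome is wrong in both possible quadrants, and it reverses the meaning of a less costly, less effective result.

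The second is conditional. If the QALY difference is also close to zero, the ICER is unstable and its sign is near a coin toss. The ranges of several hundred thousand euro per QALY rest on an assumed utility SD, cost SD and saving and on a true QALY difference of exactly zero. They are illustrations, not forecasts for this trial.

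A reader might infer that the cost-effectiveness aim cannot be interpreted at all. That goes too far: a negative ratio in the lower-cost half is dominance, which is a clear result, and the plane would show it. The point is moderate in weight. It is a correction to the analysis wording that is worth making before results are known, and it does not touch the primary outcome.

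**What to change.** In the sections Cost-effectiveness analysis (CEA) and Cost-effectiveness:

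- Report the incremental cost and the incremental QALYs separately, each with a bootstrap 95% confidence interval.
- Make incremental net monetary benefit, over a pre-stated range of willingness-to-pay thresholds, the main estimate. Give it a bootstrap 95% interval and an acceptability curve from the same samples, for both the base case and the extended analysis.
- Keep the cost-effectiveness plane.
- Report an ICER only with its quadrant named, and limit the interpretation sentence to results with higher cost and more QALYs.

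The cost is small: no new data, no added patients and no new bootstrap run. The one demand is that the thresholds be chosen in advance. The documents give none, so the 20,000 and 40,000 euro used above are not a recommendation.

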## Discussion

The aim of this study is twofold, namely investigating the effectiveness and cost-effectiveness of a blended physiotherapy program for ST, including a smartphone application designed to increase therapy compliance and provide tinnitus counselling.

The study population in scope are adult ST patients. Patients will be diagnosed with ST by a multidisciplinary team of specialists in their field. This team will exist of ENT doctors, audiologists, physiotherapists and psychiatrists. The ENT doctors and audiologists will examine the presence of possible hearing loss, underlying disorders and tinnitus. The physiotherapists will assess the presence of neck and jaw dysfunctions and the link between these dysfunctions and the tinnitus using the diagnostic criteria for somatic tinnitus [31]. Any active psychiatric disorders, such as anxiety or depression disorders, will be excluded by the psychiatrist. This extensive diagnostic process by a multidisciplinary team is a major strength of our study.

The main scientific risks associated with the present study protocol are insufficient enrolment and patient drop-out. However, every year 2500 patients suffering from tinnitus seek help at the ENT department at UZA. As a quarter of these patients are diagnosed with ST, a maximum of 625 patients will be available for inclusion in our study on an annual basis. Therefore, we expect sufficient enrolment during the inclusion period of 2.5 years. In addition, the willingness of participants to complete the full treatment program and all follow-up tests is crucial for the power of the study results. The risk for drop-out is especially high in patients who do not experience the expected treatment results. To maximise treatment adherence and minimise drop-out, patients will be encouraged to complete the treatment and follow-up phase by the therapist, the study nurse and the researcher. Nonetheless, a drop-out of 10% was considered in the sample size calculation.

This study will use a high-quality methodological design to perform a single blind two-arm randomised controlled trial. A total of 334 patients will be randomised into two groups and the current standard care will be compared to the use of a blended physiotherapy program. In studies investigating physiotherapy treatment, blinding of subjects and therapists is typically difficult. In our study, patients will be blinded towards the group they will be randomised to, but the therapist cannot be blinded, as she knows whether a patient receives the treatment every week or every 2 weeks. To limit the risk of bias related to lack of blinding of the therapist, all evaluation measurements will be performed by a blinded assessor. All physiotherapy sessions will be provided in the clinic by the same therapist. This approach was chosen to ensure all patients will receive the same treatment and to limit therapist-dependent differences in outcome in our study. This approach might decrease the transferability of our study results to a clinical situation but was deemed necessary to avoid bias.

The proposed approach of the blended physiotherapy program using a smartphone application offering both an exercise program and tinnitus counselling has never been used before in ST treatment. Similar app-based programs, however, have proven to be effective and feasible for the treatment of neck pain [69, 70]. There is also an increasing interest in the use of smartphone applications for tinnitus patients [71, 72]. This study combines both tinnitus counselling and neck/jaw treatment providing a digital application to empower ST patients to improve and better manage their own health. Earlier research has already proven that the content of the application, both the exercise program and the counselling, is effective when used in a clinical face-to-face setting [14–22, 73, 74]. However, it was never examined in the context of a smartphone application as part of a blended physiotherapy treatment. The use of our developed smartphone application is expected to help overcome common hurdles related to the in-clinic treatment of patients with ST.

In standard care, patients with somatic tinnitus receive weekly face-to-face therapeutic sessions of 30 min to reduce their neck and jaw complaints in order to also alleviate the tinnitus. On average, 9 to 12 weeks are needed to achieve the desired effect [13, 34]. In addition, patients are allways recommended to perform exercises at home. This has proven to be effective in decreasing neck pain and avoiding recurrence of the complaints, but only if patients adhere [75, 76]. Compliance to home exercises is often impeded reducing positive long-term effects of the treatment [75–80]. This is not only the case for the treatment of patients with neck complaints, but a general hurdle in musculoskeletal treatment. Reasons for low compliance to home exercises are mostly investigated in studies on low back pain but are expected to be similar for other muscoloskeletal dysfunctions [77, 79]. The most important defined barrier was ‘lack of support’, as patients indicated they did not receive sufficient instructions and follow-up to perform the exercises correctly and consistently [75, 77]. Other contributing factors are patient attitudes and beliefs, self-efficacy, locus of control, stage of change and psychosocial issues [79]. The proposed blended physiotherapy program might give answer to some of the barriers experienced by standard care. The smartphone application will change patients locus of control and promote self-efficacy by providing sufficient support and clear instructions on how to perform the exercises correctly and regurlarly. The psychological counselling provided by the app will increase the knowledge of patients about tinnitus improving patient attitudes and believes about the treatment.

The current standard physiotherapy treatment is, although effective, costly and time consuming, especially in case of recurrent complaints where patients often need several follow-up consultations and additional treatment. The longevity of the need of treatment due to recurrent complaints leads to high direct health care costs [8, 9]. Furthermore, also indirect costs, such as work absenteeism and productivity losses are high in these patients [8, 9]. Our investigated blended physiotherapy program aims to decrease the patient’s need for in-clinic treatment, without reducing the effectiveness of the treatment. The alleviation of tinnitus improves the quality of life and, as a consequence, is expected to increase productivity and reduce absenteeism. In addition, the blended physiotherapy program will reduce the need for face-to face clinical care and is expected to improve the patient's self-management skills, rather than depending on the therapist’s care in case of recurrent symptoms. All these factors are expected to contribute to a significant decrease in both direct and indirect costs due to somatic tinnitus. The proposed blended physiotherapy program has the potential to be a valuable alternative for the current standard care, with a better cost-effectiveness without decreasing the effectiveness of the treatment.

## Trial status

This is the first version of the protocol registered on 26 January 2022 at Clinicaltrials.gov: NCT05245318. The trial is currently (February 2022) in the starting phase of recruitment and is anticipated to be completed in December 2025. In case of a substantial amendment to the protocol, this will be altered through clinicaltrials.gov.

## Data Availability

As stated by the SPIRIT guidelines, the authors assure that breaking of the blind will occur at the end of the study and that data that break the blind will not be presented before release of mainline results. Data collected within the study will be disseminated to the public through scientific publications (according to the CONSORT guidelines), conferences and lectures. Results will be reported regardless of the outcome of the study. The raw data will be stored in RedCap, a secure web platform for building and managing online databases and surveys used at UZA. After publication of the results, an anonymous version of the raw data will be made available via an online repository server upon motivated request. The data management team consist of [name]. The project will also be monitored by an independent study monitoring agency. In addition, there will be an e board of General practitioners, physiotherapists, audiologists, psychologists and patients.

## Abbreviations

CATT: Cost-effectiveness of a smartphone Application for Tinnitus Treatment
ST: Somatic or Somatosensory Tinnitus
RCT: Randomised controlled trial
ENT: Ear Nose Throat
UZA: University Hospital Antwerp
TFI: Tinnitus Functional Index
HRQOL: Health-related quality of life
TMJ: Temporomandibular joint
SPIRIT: Standard Protocol Items Recommendations for Interventional Trials
FUV: Follow-up visit
EQ-5D: EuroQoL-5 dimensions
VAS: Visual analogue scale
NVA: Nederlandse Vereniging Audiologie
SPIQ: Speech in quiet
SPIN: Speech in noise
LIST: Leuven Intelligibility Sentences Test
SRT: Speech reception threshold
NBQ: Neck Bournemouth Questionnaire
TMD: Temporomandibular disorder
HADS: Hospital Anxiety and Depression Scale
HQ: Hyperacusis Questionnaire
iPCQ: Productivity Cost Questionnaire
FAHMP: Federal Agency for Medicine and Health Products
CEA: Cost-effectiveness analysis
ICER: Incremental cost-effectiveness ratio
EUnetHTA: European Network for Health Technology Assessment
RIZIV: Rijksinstituut voor Ziekte- en Invaliditeitsverzekering\
INAMI: l’Assurance soins de santé et indemnités
QALYs: Quality-adjusted life years
LoL: Length of life
